## Abstract

**Background:**

Poor body image is prevalent among adolescents and associated with several negative outcomes for their physical and psychological health. There is a pressing need to address this growing public health concern, yet there are few evidence-informed universal programmes for older adolescents that address contemporary body image concerns (i.e., social media). BodyKind is a four lesson, school-based, teacher led, universal body image programme that incorporates empirically supported principles of cognitive dissonance, self-compassion, compassion for others and social activism, to support positive body image development. Building on previous pilot trials in the USA, this paper outlines the protocol for a cluster randomised control trial (cRCT) and implementation evaluation of the BodyKind programme which was culturally adapted for the Irish cultural context.

**Methods:**

We aim to recruit 600 students aged 15-17 years in Transition Year (4^th^ year) across 26 second-level schools in Ireland. Using minimisation, schools will be randomly assigned to receive BodyKind (intervention condition, *n=*300) or classes as usual (waitlist control, *n=*300). Teachers in intervention groups will receive training and deliver the programme to students over four weeks, at a rate of one lesson per week. Primary outcomes of body appreciation, body dissatisfaction and psychological wellbeing and secondary outcomes of self-compassion, compassion for others, body ideal internalisation, social justice motives and appearance-based social media use will be assessed at pre-, post- and 2 month follow up. Mediation and moderation analyses will be conducted to identify how and for whom the intervention works best. An implementation evaluation will assess the quality of programme implementation across schools and how this may influence intervention outcomes. Waitlist control schools will receive the programme after the 2-month follow up.

**Conclusion:**

This study will be the first to implement a cRCT and an implementation evaluation to assess the impact of this multicomponent school-based body image programme designed to support healthy body image development. If shown to be effective, BodyKind will have the potential to improve adolescent body image and wellbeing and inform efforts to implement sustainable and scalable programmes in schools.

**Trial registration:**

The trial was retrospectively registered on 10/10/2023 on ClinicalTrials.gov NCT06076993.

**Supplementary Information:**

The online version contains supplementary material available at 10.1186/s12889-023-17002-x.

## Background

Body image concerns are prevalent among adolescents, with an estimated 75% of young people reporting body image distress worldwide [1]. Body image concerns are associated with several negative outcomes for physical health [disordered eating/exercise [2, 3] and psychological wellbeing [low self-esteem, negative affect [3, 4] and are a primary modifiable risk and maintenance factor for eating disorders [5, 6]. Body image concerns and eating disorders have increased over the last decade [1, 7], particularly since the Covid-19 pandemic, with some studies reporting almost a doubling in the incidence of eating disorder related care in 2019 for adolescents compared with previous years [8–10]. Similarly in Ireland, less than half of adolescents are satisfied with their appearance [11] and a 66% increase in acute hospital admissions for eating disorders was observed among young female adolescents in Ireland between 2019-2020 [12]. Effective prevention is required to reduce the burden of disease and support adolescent psychological wellbeing [13]. Universal eating disorder prevention, which addresses all levels of risk, are often delivered in schools as they provide a cost-effective and inclusive way to access a wide range of adolescents within a sustained, learning environment [13, 14].

Traditionally, eating disorder prevention approaches have targeted risk factors for body image concerns [15], such as body ideal internalisation [i.e., cognitively endorsing body ideals as personal body standards [16] and appearance comparisons [i.e., comparing oneself on dimensions of appearance [17], which according to the Tripartite Model of Body Image [18], mediate the relationship between sociocultural appearance pressures (e.g., social media, peers, family) and the development of body image concerns. There is considerable evidence that such cognitive dissonance approaches [19], which involve publicly criticising unrealistic body ideals reduce the pursuit (internalisation) and comparison with these ideals, are effective in reducing adolescent body dissatisfaction in school-based trials [14, 15, 20, 21].

Recently, prevention approaches have acknowledged the importance of promoting positive body image, in addition to countering body dissatisfaction [22]. Positive body image, which is operationalised as body appreciation, is a unique, holistic construct which involves respecting, appreciating, nurturing and caring for one’s body and honouring natural body diversity [23], and is independently associated with benefits for physical and psychological health [e.g., greater adaptive coping, life-satisfaction, self-care behaviours [22–24]. Self-compassion represents a promising approach for supporting body appreciation and psychological wellbeing [25, 26]. Self-compassion is an emotional regulation strategy [27] that enables individuals to self-soothe by reframing self-critical thoughts and shame that are at the root of body dissatisfaction [28]. Self-compassion also helps individuals to appreciate alternative aspects of themselves (rather than overvaluing appearance) to promote positive body image [27, 29]. Self-compassion interventions are found to be effective in supporting adolescent psychological wellbeing [30, 31] and there is growing evidence that they show promise for improving body appreciation in adolescents [32–34].

Additionally, social justice perspectives [35], advocate that eating disorder prevention should move beyond the individual, to target the broader structural and social inequities inherent in diet culture that initiate and perpetuate appearance concerns in the first place [36]. Within the classroom context, where peers are present, empowering adolescents to challenge appearance biases (where people are treated differently based on how they look versus how they are as a person) and to engage in prosocial, compassionate behaviours towards others, such as challenging peer norms or reducing body talk/body shaming, could represent an approach to develop a supportive context for positive body image development [37–40]. However, further research on social justice motives and prosocial body image behaviours as pathways to building positive body image in adolescents are required [37].

While progress has been made in school-based body image intervention approaches, many gaps remain; firstly, most existing evidence-based programmes target early adolescents (12–13-year-olds), but there are fewer programmes that address body image concerns of older adolescents, despite the finding of the peak onset of eating disorders is between mid-late adolescence [41, 42]. Additionally, many existing programmes fail to address contemporary adolescent body image concerns, such as social media-related concerns [although there are exceptions [43, 44], or do not focus on the body image concerns of males and adolescents across the gender spectrum [15]. Also, many interventions are researcher-led, and there is a need for scalable and self-sustainable effective programmes that are teacher-led and that work towards building contexts to support positive body image development [36, 45].

Be Real’s BodyKind is a four-session, teacher-led, gender-inclusive school-based programme for adolescents aged 15-17 years that targets contemporary body image issues for adolescents (e.g., social media, gender inclusivity). This multicomponent intervention combines, for the first time, empirically supported principles of cognitive dissonance, self-compassion and social activism and is anticipated to enhance body image outcomes by facilitating various mechanisms of change to occur [outlined elsewhere in a Logic Model [46]. BodyKind was originally developed for high schools in the USA, with goals for broader, global implementation should the programme prove efficacious. Preliminary trials in the USA indicate the acceptability and feasibility of the BodyKind programme [46]. To facilitate the next phase in the development/evaluation of complex interventions, a rigorous cluster randomised trial cRCT evaluation across multiple sites is required [47].

To this end, BodyKind was culturally adapted to the Irish context via a series of codesign workshops with adolescents (*n=*12, 15-16 years) and interviews with teachers (*n=*6) and a clinician (*n=*1) to optimize intervention effects [48]. After receiving the BodyKind programme, students shared perceptions of programme acceptability and codesigned content to ensure its cultural relevance to the Irish context (e.g., examples/scenarios that are relevant for young people in Ireland) [49, 50]. Teacher feedback was used to facilitate implementation in schools (i.e., scheduling content delivery across 40–60-minute class durations, and to ensure content aligned with the Department of Education and Skills Wellbeing Policy Statement and Framework for Practice). The programme was considered highly acceptable by teachers and students, with 82% of students stating that they enjoyed the lessons and 73% would recommend the programme to a friend. A female clinician from Jigsaw, The National Centre for Youth Mental Health, was also consulted to ensure the programme aligned with Jigsaw’s ethos for supporting youth mental health in Ireland. Cultural adaptation protocols and details of changes made to the programme are outlined elsewhere.

The current paper describes the protocol for a cluster randomised control trial cRCT, which will be conducted in Irish schools with 4th year second-level students (aged 15-17 years) to evaluate the effectiveness of the culturally adapted BodyKind programme in improving body image and mental health outcomes among adolescents in Ireland. Schools will be randomly assigned to intervention or waitlist control conditions [14, 43]. Teachers in the intervention condition will complete 2.5 hours of training and will deliver the programme to students. Primary outcomes of body image and psychological wellbeing, and secondary outcomes of broader body image risk and protective factors will be assessed at three time points (pre, post, two-month follow up). Mediators, (i.e., active ingredients of interventions, e.g., self-compassion) and moderators (i.e., factors that change the strength of effects, e.g., implementation quality) will also be explored to understand how and for whom the intervention works best.

In addition to examining effectiveness, best practice guidelines in school-based research increasingly emphasise the importance of conducting implementation evaluations to assess how well programmes are delivered in schools and if programmes are delivered as intended [49, 51, 52]. Implementation evaluations are essential for providing insights into factors that may lead to a programme’s success or failure [51]. They can also inform efforts to guide sustainable delivery of programmes in schools. Thus, a mixed methods evaluation of implementation quality will be conducted to understand ‘why’ programme outcomes were observed and to inform efforts to optimise programme delivery in schools in the future. Aligning with previous studies [52, 53], the quality of implementation of BodyKind in schools will be assessed across four key implementation dimensions: (i) dosage, (ii) adherence, (iii) quality of delivery, and (iv) participant responsiveness.

This study will be the first to implement a cRCT design and implementation evaluation to examine BodyKind – an innovative, gender-inclusive, culturally sensitive programme designed to improve adolescents’ body image and psychological wellbeing. This research is anticipated to provide novel contributions to school-based body image intervention work.

We hypothesise that 1.) Compared to participants in the waitlist control, participants who receive the BodyKind programme will experience statistically significant increases in a.) body appreciation, psychological wellbeing, self-compassion and compassion for others and other’s bodies, social justice motivations and b.) significant decreases in body dissatisfaction and body ideal internalisation from pre- to post-intervention. 2.) Changes will be maintained in intervention groups at a 2-month follow up. 3.) Changes in body appreciation and body dissatisfaction will be mediated by self-compassion, compassion for others and body ideal internalisation. We make no a-priori assumptions about the directionality of mediation effects. 4.) Changes in body appreciation, body dissatisfaction and psychological wellbeing will be moderated by appearance-related social media use, appearance teasing, gender, baseline body appreciation, body dissatisfaction, psychological wellbeing and implementation quality. We make no a-priori assumptions about the directionality of moderation effects.

A mixed methods evaluation (non-directional) will be conducted to determine schools’ quality of implementation of BodyKind across key implementation dimensions. We expect that the programme 5.) will be considered acceptable and feasible by adolescents and teachers , 6.) can be implemented with high fidelity by teachers and that 7.) implementation quality may vary across schools and this may impact intervention effectiveness.

## Method

### Design

This study will use a parallel two-arm cluster randomised control trial (cRCT) with equal allocation of schools to intervention or waitlist control conditions (see Fig. 1). Teachers in schools assigned to the intervention condition will receive training and will deliver the BodyKind programme to students, while the waitlist control will receive classes as usual. This will be a pragmatic trial, conducted under ‘real world’ conditions i.e., in a school setting, with teacher-led delivery during class time over a four-week period (1 lesson each week). Outcomes will be measured at three time points (pre-, post- and two-month follow up). As per [54], a two-month follow up was selected to fit within the academic school year. Waitlist control schools will complete teacher training and the BodyKind programme after the completion of measures. This study received ethics approval from University College Dublin University (HS-22-71) and was retrospectively registered on 10/10/2023 on ClinicalTrials.gov, NCT06076993.

**Fig. 1 Fig1:**
[figure not shown]
CONSORT recruitment diagram

### Participants

We aim to recruit a total of 600 students aged 15-17 years in Senior Cycle: Transition Year (a non-academically structured year in Irish secondary schools designed to facilitate the pursuit of alternative interests and self-discovery). An RMASS power analysis [55] based on parameters; small Cohen’s d effect size of .2, power .80, alpha .05, indicates that 504 students are required. A small effect size was selected in line with a meta-analysis of schools-based interventions for body image outcomes [14] which observed small effect sizes (d=.22 - .48) which despite being described as ‘small’ can have important real-world impact, particularly when scaled up across a whole school population [56]. To account for natural attrition and unanticipated events that reduce participant numbers (e.g., student absence due to illness) in cRCTs, we will recruit approximately 20% (*n=*100) more participants giving a total *N=*600. Given the variability in class size in Transition Year range in consent rates for active parental consent [57], and to guard against drop out at a cluster level we will recruit a minimum of 12 schools and a maximum of 26 schools with 1-2 fully qualified second-level teachers per school (range 12-52 teachers). Schools will be eligible if they are a second-level school in the Republic of Ireland that offers the Transition (TY) programme to students. Only data from full-time TY students aged 15-17 years (i.e., not exchange or short-term visiting students) will be included in analyses.

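### The 504 students said to give 80% power do not follow from the inputs listed, and the figure is tied to no number of schools although 12 to 26 are allowed

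*Protocol article*

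**What the plan says.** In the protocol article, Method, Participants, a power program for repeated-measures designs is cited with three parameters and one result: "effect size of .2, power .80, alpha .05, indicates that 504 students are required". The effect size is supported by a meta-analysis that "observed small effect sizes (d=.22 - .48"). The total is then raised by about a fifth, to 600: "To account for natural attrition and unanticipated events that reduce participant numbers".

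The number of schools comes afterwards: "we will recruit a minimum of 12 schools and a maximum of 26 schools". The reasons given are varying class size, varying consent rates and drop-out of whole schools. Power is not mentioned in that sentence.

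Elsewhere, Design states that schools are the randomised unit, allocated equally. The Abstract and the Recruitment and randomisation section work with 26 schools. Data analyses says clustering will be handled at school level and that the primary comparison is baseline against post-intervention. The only ICC mentioned there is one to be estimated from the trial data. The Abstract names three primaries: "Primary outcomes of body appreciation, body dissatisfaction and psychological wellbeing".

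**The concern.** Two features of the sample-size statement do not fit together. First, the three listed inputs describe a plain two-group comparison, and 504 is well below what such a comparison needs. Second, in a school-randomised trial the power from a fixed number of students depends on how many schools they are spread over. The article quotes one required number and then permits a more than two-fold range of schools.

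The trial could therefore go ahead at its stated minimum of 12 schools on the understanding that it has 80% power for an effect of .2, when under modest clustering the true figure may be much lower. A null result would then be read as stronger evidence against a small effect than it is. Nor can a reader tell which of the three primary outcomes the stated power and alpha refer to.

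**Working it through.** **Inputs from the article (Participants):** d = .2 (SD = 1 on the standardised scale), power .80, alpha .05, 504 required, 600 recruited, 12 to 26 schools. Sidedness, ICC and pre-post correlation are not given. ICCs of .01, .02 and .05 are assumptions used to show a range.

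**Step 1. Try to reproduce 504.** For two equal groups, the total is N = 4(z_alpha + z_power)²/d².
- Two-sided: 4(1.960 + 0.842)²/.04 = 784.9, so 393 per arm, 786 in total.
- One-sided: 4(1.645 + 0.842)²/.04 = 618.3, so 310 per arm, 620 in total.

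Neither gives 504.

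**Step 2. What would give 504?** The ratio 504/784.9 is .642. With clustering ignored:
- Baseline-adjusted analysis: 1 − r² = .642, so r = .60.
- Change score: 2(1 − r) = .642, so r = .68.

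Both are plausible, but neither is stated. Other combinations that include an ICC and a higher correlation are also possible.

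**Step 3. Dependence on the number of schools.** The design effect is DE = 1 + (N/k − 1) × ICC for k schools. At N = 504 the mean cluster is 42.0 students with 12 schools and 19.4 with 26.

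| ICC | DE, 26 schools | DE, 12 schools |
|---|---|---|
| .01 | 1.18 | 1.41 |
| .02 | 1.37 | 1.82 |
| .05 | 1.92 | 3.05 |

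These differ for every ICC above 0, so the required N differs too.

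**Step 4. Power for d = .2 under three readings of 504.** Non-centrality is λ = .2/√(4 × f × DE/N), where f is the variance factor from repeated measures. The test is a two-sided t on k − 2 df (critical values 2.064 for 24 df and 2.228 for 10 df).

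*Reading A: 504 ignores clustering* (f = .642), all 600 analysed. DE is 1.22/1.44/2.10 at 26 schools and 1.49/1.98/3.45 at 12. λ is 2.77/2.55/2.11 and 2.50/2.17/1.65.

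*Reading B: 504 is exact at 26 schools.* 80% on 24 df needs λ = 2.92. At 12 schools with 504 analysed, λ = 2.92 × √(DE at 26 / DE at 12) = 2.68/2.53/2.32.

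*Reading C: 504 was sized for 12 schools.* 80% on 10 df needs λ = 3.11. At 26 schools with 504 analysed, λ = 3.11 × √(DE at 12 / DE at 26) = 3.39/3.59/3.92.

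| Reading | Schools | Analysed | ICC .01 | ICC .02 | ICC .05 |
|---|---|---|---|---|---|
| A | 26 | 600 | 76% | 69% | 53% |
| A | 12 | 600 | 62% | 50% | 32% |
| B | 12 | 504 | 67% | 63% | 55% |
| B | 12 | 600 | 73% | 67% | 57% |
| C | 26 | 504 | 90% | 93% | 96% |

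Under A with 600 analysed, the effect detectable with 80% power for ICC .02 to .05 is about .23 to .28 at 26 schools and .29 to .38 at 12.

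Under C, 504 is more than is needed at 26 schools. By the normal approximation at ICC .01, the unclustered requirement is 504/1.41 = 357, and the number needed at 26 is 357 × .99/(1 − 357 × .01/26) = 410. For ICC .02 and .05 it is 345 and 230.

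**The case against.** The strongest defence is that 504 is unreproducible, not shown to be false. The article cites a repeated-measures power program whose run is not visible. The trial has several time points, and a condensed article may leave out inputs. The plain two-group 786 is not the trial's own analysis. This stands, so the criticism is of what the stated inputs support.

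A reader might go further and infer that the design lacks 80% power, or that the claim cannot be true at both ends of the range. The article does not support that. If 504 was sized for 12 schools, power is 80% there and about 90% or more at 26, and nothing in the text excludes this. Nor does the article say outright that 12 schools give 80%, since the range is justified by class size, consent and drop-out. Still, a stated minimum beside a single required number invites that reading.

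The ICCs are assumptions. Stable school differences largely cancel in a Time by Condition contrast, and allocation is constrained on the numbers of boys and girls and on location, so the relevant ICC could be near the low end. The .05 column should not be treated as expected.

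Two further inferences should be resisted. Going from 504 to 600 absorbs 1 − 504/600 = 16% loss, but the text speaks of about 20% more participants (504 × 1.2 = 605) and states no 20% loss rate, so this is not an error. Error control across the three primary outcomes may sit in an analysis plan that is not shown, so its absence here is not a fault. What remains is that the alpha and power used for sizing are not linked to any of the three.

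**Conclusion.** The point holds as a defect in the sample-size statement. The listed inputs give about 786 (two-sided) or 620 (one-sided) before clustering, not 504, so the figure rests on inputs the reader cannot see. Independently of what those inputs were, one number cannot be the requirement at both 12 and 26 schools once the ICC exceeds 0, which the trial's own clustered analysis anticipates.

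The size depends on how 504 was obtained. For ICC .01 to .05, power at 12 schools ranges from 62% down to 32% if clustering was ignored (600 analysed), and from 67% down to 55% if 504 is exact at 26 schools (504 analysed; 73% down to 57% with 600). It is 80% if 504 was sized for 12. At 26 schools the corresponding figures are 76% down to 53%, 80%, and about 90% or more. These rest on assumed ICCs, equal cluster sizes and t-tests on schools minus 2 df. They show that the stated 80% cannot be relied on as written, without establishing that it is wrong.

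**What to change.** Restate the calculation in Participants:
- Give the ICC, pre-post correlation, number of time points, sidedness and number of schools used in the program run.
- Report power for d = .2 and the effect detectable with 80% power at both 26 and 12 schools, saying whether 504 or 600 students are assumed analysed.
- Do not attach 80% power to the 12-school minimum unless the recalculation supports it. The 26 schools in the Abstract are the natural basis for the main figure.
- Say which primary outcome or outcomes the alpha of .05 and the stated power refer to.

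The cost is a recalculation and one paragraph. No additional students or schools are needed. The quoted power may become less favourable, particularly at the lower end of the school range.
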